#### Secondary endpoints

The precursors of ulceration are analyzed analogously to the primary endpoint.

The score values of the quality of life at the different time points are analyzed by means of mixed models for repeated measurements, whereby the four stratification factors from randomization (risk group, gender, age and the degree of neuropathy) are also included as influencing variables in addition to the therapy arm. The main comparison refers to the time of 24 months.

AEs and SAEs are recorded separately by treatment arm and risk class. In logistic regression models, a comparison between the therapy arms (insofar as the type of AEs/SAEs is not coupled to the experimental therapy arm) is made with the occurrence of at least one event per patient as the target and the same influencing variables as in the analysis of the primary endpoint.

The usage data of the insoles and the corresponding app are first extracted for the patients of the experimental arm from the automatic machine recordings and aggregated in the sense of the corresponding secondary endpoints ([name]. med. [name], Institute for Biometry and Medical Informatics, Otto-von-Guericke-University Magdeburg).

All analyses are carried out using the software packages SAS or SPSS.

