**Fig. 1 Fig1:**
[figure not shown]
Algorithm for possible study enrollment, with description of the inclusion, exclusion and termination criteria of the study in the screening process

In a next step, patients will be randomized into control or intervention group in a ratio of 1:1. Two weeks later, at visit 0, they will be trained by a qualified study physician about regular foot care measures to prevent foot ulcers (standardized patient education) (see Additional file 2). The non-intervention group will not undergo any further immediate intervention; however, research participants in this group will be seen at regular follow-up visits at six-month intervals (Fig. 2). In the intervention group, every patient receives a pair of slippers with inserted sensor-equipped insoles as well as a smartphone with a Smart Prevent Diabetic Feet Application (SPDFA) (Fig. 3, see Additional file 3). They will perform measurements of their foot temperatures twice a day at home, with time intervals > 4 h during the entire study course, which comprises 24 months. In case of temperature differences > 1.5 °C between left and right corresponding sensor sites, and lasting > 32 h, the study participant will be instructed to reduce daily activities and relax his feet for five days. Additionally, the participant will receive a notification by the app to take pictures with his smartphone from the dorsal and (possibly with help of care providers) plantar feet that are transferred to the study center. In the app, essential guidance and foot masks help the patient to capture standardized foot images (Fig. 5). Depending on the findings of the photo documentation, additional visits to the study center to perform clinical examinations will be arranged for the patient during this intervention period.

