**Fig. 3 Fig3:**
[figure not shown]
Study materials for patients in the intervention group showing the sensor-equipped insole (Medixfeet Insole®, Thorsis Technologies GmbH) and the Smart Prevent Diabetic Feet Application (SPDFA)

In addition, patients in both groups are required to consult a physician when early signs of foot ulceration are noted by self-inspection of the feet (e.g. redness, pain, sores). Follow-up visits are carried out after enrollment in the study at months 6, 12, 18, and 24 by a registered nurse and a physician trained to diagnose and treat DFS. Visits 1 and 3 (after 6 and 18 months, respectively) encompass the evaluation of patient’s foot status, control of unexpected events, summary of endpoints, and assessment of the collected sensor data. Visits 2 and 4 (after 12 and 24 months, respectively) additionally include the assessment of outcome measures, patient’s wellbeing evaluation by WHO-5-questionaire, as well as taking pictures with normal illumination and infrared light from the patient’s feet (Fig. 2).

The primary endpoint of the study is DFU formation (more precisely, the time until ulcers form) and the total number of ulcerations in each group. Secondary endpoints will include evaluation of AEs and SAEs, precursors of the primary endpoint as listed above, assessment of quality of life using an interactive patient’s diary (Fig. 6), patient compliance, information about temperature alarms—including “slow” temperature drops, and acquisition of photo documentation.

If a foot ulcer occurs in a patient, it will be treated according to the usual measures of standard clinical care. Possible discontinuation of the study occurs according to the defined termination criteria (Fig. 1).

The SPDFA receives the measured data of the sensor-equipped insole via low-energy Bluetooth® connectivity. It then performs an initial analysis of temperature differences and visualizes these. Thereafter, the temperature recordings are transferred from the SPDFA to a study server. This server is located in the premises of the computer center of the Medical Faculty of the Otto-von-Guericke University Magdeburg. The data may be exported from the study server in a suitable format (SAS / SPSS) for statistical analysis at the Institute of Biometry and Medical Informatics. The final report will be compiled no later than one year after the end of the study.

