**Fig. 6 Fig6:**
[figure not shown]
*Flow diagram* on health self-evaluation within the SPDFA. The interactive wellbeing score is based on the standard WHO-5 questionnaire30, which contains five items: mobility, self-care, usual activities, pain/discomfort, and anxiety/depression. Additionally, the assessment of foot status helps the patient to record the precursors of ulcer development, such as redness, blister formation, pressure sores, lacerations, pain, inflammation, and any other wounds

In contrast, on the SPDFA, the patient will be reminded to perform foot inspection and temperature measurements at every alarm level. At the respective alarm levels (1–3), the patient will receive a classification result as “uneventful.” Then, at alarm level 3, the patient will be asked to take a photo series (four images; of each foot from the plantar and dorsal sides; Fig. 5). At alarm level 4, the patient will be informed that his measurements will be interpreted remotely by the physician. If the physician recommends an intervention from the server, the patient will be continuously informed to relax his foot and to reduce daily activities for five days. The patient will also be requested to confirm that he follows the advice to relax his feet and reduce daily activities with an interactive dialog and a countdown sequence.

Following the five-day intervention, the physician will evaluate the collected data together with the patient’s feedback and the foot images taken on the last day during this period. Depending on this evaluation, the physician will determine whether another intervention period is required or if a doctor’s visit is needed.

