### Outcome measures

#### Primary outcome measure

The primary outcome is occurrence of foot ulceration at any point during the 24-month study after visit 0. The severity level of foot ulcerations is classified according to the Wagner-Armstrong classification [30]. Any lesion will be considered as an ulcer in the sense of the primary endpoint (≥ Wagner level 1). Primary endpoints are also assessed according to time to onset of event and to the total number of events (ulceration) in the groups.

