#### Secondary outcome measures

The following have been defined as secondary outcomes:
Adherence to the daily two-time temperature measurement based on data acquisition with the appReport on alert frequency in the intervention group based on data acquisition with the appDetection of slow temperature drops as an indicator of blood supply disorders (at daily intervals temperature changes are recorded and evaluated by the study physician: when temperature in the forefoot or whole foot drops considerably compared to the contralateral sensor data (> 1.5 °C) and reach ambient temperature levels an additional visit to the study center will be initiated to test for changes of blood supply) safety-relevant instructions concerning diabetes, the equipment (insole) or others that are evaluated by the study protocol: frequency of AEs and SAEsPrecursors of the primary endpoint: redness, infections, or wounds in the foot area (the precursors are recorded by AEs/SAEs reports, follow-up and unscheduled visits, as well as patient’s report through photo documentation of the SPDFA)Quality of life according to the WHO-5 score [31, 32] at visits 1, 2, 3, and 4

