### Statistical analysis

#### Primary endpoint

The primary endpoint “time to onset of the first ulcer” will be analyzed using Cox regression for the intention-to-treat population. Regressors are the treatment arm, age (in years), gender, risk class, and degree of neuropathy. The decisive test is the test adjusted to the other influencing variables for the influence of the therapy arm (a = 0.05, two-sided). The adjusted hazard ratio of the treatment, including a 95% confidence interval, is calculated as the corresponding effect estimator. Secondary analyses pertain to the same analysis but in the per-protocol population.

In addition, in the intention-to-treat population, the ulceration rates for both treatment arms and the associated odds ratio are determined using the Mantel-Haenzel test with the risk class as stratification, whereby the patients are included in the analysis regardless of the actual follow-up period. In addition, the highest Wagner classifications of an ulceration observed for each patient (possibly 0 if no ulceration) are compared between the two therapy arms using the Mann–Whitney U-test, whereby these analyses are performed separately for the two risk classes.

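### Ulcer precursors are compared between arms although the app, and the visits it triggers, record them in the intervention arm only, so the hazard ratio leans against the intervention

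*Protocol article*

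**What the plan says.** Secondary outcome measures lists redness, infections and wounds in the foot area as precursors and states how they reach the data: "the precursors are recorded by AEs/SAEs reports, follow-up and unscheduled visits, as well as patient’s report through photo documentation of the SPDFA".

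The app belongs to one arm. Under Study design, the intervention group receives slippers with the insoles and a smartphone carrying the app, while the control group has no further immediate intervention and is seen every six months. The caption of Fig. 3 describes "Study materials for patients in the intervention group showing the sensor-equipped insole" and the app. In the Fig. 6 caption, "the assessment of foot status helps the patient to record the precursors of ulcer development", so the app diary invites self-report of the same signs.

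For the analysis, Statistical analysis, Secondary endpoints, states: "The precursors of ulceration are analyzed analogously to the primary endpoint". The model referred to is given under Primary endpoint: "The primary endpoint “time to onset of the first ulcer” will be analyzed using Cox regression for the intention-to-treat population". It is adjusted for the stratification variables, and the treatment hazard ratio is the effect estimate.

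The same subsection limits the between-arm comparison of adverse events to types that are not tied to the experimental arm. It sets no such limit for precursors.

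**The concern.** A between-arm hazard ratio measures a treatment effect only if an event has the same chance of being recorded in both arms. Here one source does not exist for controls, and another, unscheduled visits, is fed by app photos and alarms in one arm only. A redness that fades within days can enter the data of an intervention patient through a requested photo. In a control patient it is recorded only if the patient notices it and consults a physician, or if it reaches the study as an adverse event.

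Precursors are where a monitoring intervention might be expected to show how it works. If the device reduces them, the planned analysis may show a weaker effect or none. If it does nothing, the analysis may suggest harm. In either case the estimate mixes the effect of the intervention with how closely each arm was observed.

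**Working it through.** **1. Recording routes by arm**

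| Route | Intervention | Control | Where stated |
|---|---|---|---|
| Examination and interview at 6, 12, 18, 24 months | yes | yes, the same | Control group |
| Self-inspection, then physician consultation | yes, with app reminders at every alarm level | yes, no app reminders | Study design; Intervention |
| Adverse event reports | yes | yes | Secondary outcome measures |
| Photo series requested at alarm levels 3 and 4 | yes | no | Intervention |
| App diary of foot status | yes | no | Fig. 6 caption |
| Extra visits after photo findings or temperature drops | yes | no | Study design; Secondary outcome measures |

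Three routes are shared, one of them with extra prompting in one arm. Three exist in one arm only. Removing the photos alone would not equalise the arms, because the extra visits remain.

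**2. Illustration of size**

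The plan states no figure for precursors, so there is none to reproduce. From Sample size: 150 per arm and 20% drop-out, hence 150 × 0.8 = 120 evaluable per arm. From Primary endpoint: two-sided 5% level. Everything else is assumed:

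- p = true 24-month precursor risk in controls: 0.2, 0.4, 0.6
- s = fraction caught by the shared routes: 0.5, 0.7
- a = fraction of the remainder caught by the app or its visits, intervention arm only: 0.2, 0.4, 0.6

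With no true effect:

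- Recorded risks: control ps; intervention p(s + (1 − s)a)
- Apparent HR = ln(1 − intervention risk) / ln(1 − control risk)
- Events D = 120 × (sum of recorded risks); z = √(D/4) × ln HR; rejection rate = Φ(z − 1.96) + Φ(−z − 1.96)

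One cell in full (p = 0.4, s = 0.5, a = 0.4):

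- Recorded risks: 0.4 × 0.5 = 0.20 and 0.4 × 0.7 = 0.28
- HR = ln 0.72 / ln 0.80 = 1.47
- D = 120 × 0.48 = 57.6, z = 1.47, rejection rate about 31%

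All cells, as apparent HR with the rejection rate in brackets (nominal 5%):

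| s | a | p = 0.2 | p = 0.4 | p = 0.6 |
|---|---|---|---|---|
| 0.5 | 0.2 | 1.21 (8%) | 1.23 (12%) | 1.25 (17%) |
| 0.5 | 0.4 | 1.43 (16%) | 1.47 (31%) | 1.53 (50%) |
| 0.5 | 0.6 | 1.65 (29%) | 1.73 (58%) | 1.83 (84%) |
| 0.7 | 0.2 | 1.09 (6%) | 1.10 (7%) | 1.12 (9%) |
| 0.7 | 0.4 | 1.19 (8%) | 1.21 (13%) | 1.24 (21%) |
| 0.7 | 0.6 | 1.28 (12%) | 1.32 (23%) | 1.38 (40%) |

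With a = 0 the HR is 1.00 and the rejection rate 5%.

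**3. If there is a true benefit**

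For an assumed true HR of 0.6, the intervention arm's true risk becomes 1 − (1 − p)^0.6. Over the same grid the apparent HR runs from 0.66 to 1.16. With a = 0 it is 0.61 to 0.67, so a little of the shift comes from incomplete capture in both arms and the rest from the unequal routes.

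For a larger effect, take 1/2.8, which is the ulcer effect in Sample size and is only assumed to carry over to precursors. With p = 0.4 and capture of 0.50 in controls against 0.625 to 0.75 in the intervention arm, the true risk is 1 − 0.6^(1/2.8) = 0.167. The apparent HR is then ln(1 − 0.104)/ln 0.80 = 0.49 to ln(1 − 0.125)/ln 0.80 = 0.60, instead of 0.36.

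**4. Earlier recording alone**

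A Cox simulation (400 runs, 150 per arm, p = 0.4, no true effect) let every precursor persist until the next six-monthly visit, so the app changed only the recorded date. With the app catching 25%, 50% or 100% of precursors at onset, the HR was 1.02, 1.04 and 1.09, and rejection was 4%, 6% and 7%. The larger bias therefore needs transient precursors seen only through the app or a visit that it triggers.

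**The case against.** The strongest reply is that the statistical sentence names a method and does not say which records count as events. A full protocol or analysis plan could restrict the sources, and nowhere does the article say that an unverified photo starts an event. The diary is not itself listed as an endpoint source. This tempers certainty about the final analysis, but the point stands: the article itself defines the endpoint by its recording routes and fixes the between-arm comparison, and it limits the adverse event comparison but not this one.

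The shared routes are also real. Patients in both arms must consult a physician on early signs, and controls receive foot-care support and the same visits. Photos are requested only at the two highest alarm levels. All this shrinks the imbalance. It does not close it, since the app also prompts foot inspection in one arm.

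A reader might infer that the intervention will look harmful. The documents do not support that: they give no precursor risk or capture rate, and with a true benefit the more likely result is attenuation. A reader might also object that foot wounds are precursors while "Any lesion will be considered as an ulcer in the sense of the primary endpoint" from Wagner level 1 upwards, so that one wound counts twice. Precursors and ulcers are separate endpoints analysed separately, so no analysis counts it twice. Whether to exclude such wounds is a matter of definition and forms no part of this point.

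**Conclusion.** Followed as written, the precursor comparison has unequal ascertainment, and its hazard ratio is biased against the intervention. The direction needs only that the app or its visits catch some precursors that the shared routes miss. The size cannot be derived from the documents. Over the assumed grid, no true effect appears as a hazard ratio of about 1.1 to 1.8, with rejection rates of about 6% to 84% in place of 5%; a true hazard ratio of 0.6 appears as 0.66 to 1.16. These are illustrations, not predictions.

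A reader might take this as undermining the trial's main result. It does not: the decisive test is the Cox model for the first ulcer, which this sentence leaves alone, and a bias in this direction would not produce a false claim that precursors are reduced. The change should be made, but the trial does not stand or fall by it.

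**What to change.** - Flag the source of every precursor record: scheduled examination, interview, patient-initiated consultation, adverse event report, app photo or diary, alarm- or photo-triggered visit.
- Base the main between-arm comparison on precursors found at the identical 6-, 12-, 18- and 24-month examinations. Because times are then grouped in six-month steps with many ties, use a discrete-time model with complementary log-log link, or an interval-censored model, with the same covariates.
- Report app- and alarm-detected precursors descriptively, in the intervention arm only.
- Keep the all-source Cox analysis as a sensitivity analysis, labelled as subject to differential ascertainment.

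The cost is analysis-plan wording and one data field; treatment, visits and sample size do not change. Two drawbacks should be stated. Precursors that resolve between visits leave the main comparison, including those seen at consultations that both arms are asked to seek. And because the trial is open-label and one arm has been prompted throughout, what patients report at interview may still differ by arm, so examination findings should carry the comparison.

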### Secondary specific aims

The secondary objectives of the present study were to:
collect safety-relevant information concerning the equipment (insole)
frequency of adverse events (AEs)frequency of serious adverse events (SAEs)quantify precursors of the primary endpoint
redness in the foot areainfections in the foot areawounds in the foot areaevaluate the changes of quality of life independent of primary and secondary endpointsassess the adherence to daily two-time temperature measurements based on data acquisition by the apprecord the alarm frequency in the intervention group based on data collected by the appdetect “slow” temperature drops as an indicator of circulatory disordersassess the adherence to photo documentation

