### Sample size

Based on previously reported studies, we assumed a 20% ulcer occurrence rate over two years to be a conservative estimate for the control arm (where in case of a higher occurrence rate, the sample size becomes smaller) [15, 33, 34]. For the estimation of the treatment effect, we assumed a hazard ratio of 2.8 in accord with the study of Armstrong et al. [15]. Sample size calculations by use of log-rank test were based on a type I error probability of 5% (two-sided) and a power of 80%, with a drop-out rate of 20% over a two-year follow-up period per patient. This resulted in a calculated required number of cases of 147. Therefore, we plan for an inclusion of 150 patients for the intervention arm (300 patients in total). Sample size calculation was performed using the software nQuery + nTerim 4.0 (Statistical Solutions Ltd., 2015).

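### The formal between-arm comparison of general AEs and SAEs uses only 'at least one event per patient', so it ignores repeat events and follow-up time; add an event-rate comparison beside it

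*Protocol article*

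**What the plan says.** Secondary specific aims lists the "frequency of adverse events (AEs") and of SAEs among the safety objectives, and Secondary outcome measures repeats this. The document does not define frequency as a share of patients or as events per unit of time.

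Statistical analysis, Secondary endpoints, then fixes three things:

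- Reporting: "AEs and SAEs are recorded separately by treatment arm and risk class".
- Comparison: logistic regression "with the occurrence of at least one event per patient as the target and the same influencing variables as in the analysis of the primary" outcome (treatment arm, age, gender, risk class, degree of neuropathy).
- Scope: the comparison is made "insofar as the type of AEs/SAEs is not coupled to the experimental therapy arm".

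The section names no count model, rate or follow-up term for AEs or SAEs. It does give one group of foot events another analysis: "The precursors of ulceration are analyzed analogously to the primary endpoint", that is, by Cox regression. Secondary outcome measures says of redness, infections and wounds that "the precursors are recorded by AEs/SAEs reports, follow-up and unscheduled visits", among other sources.

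Sample size plans for 150 patients per arm and 20% dropout over two years.

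**The concern.** Over 24 months a patient can have several AEs, and all after the first drop out of the comparison. For all AEs pooled, in patients aged up to 85 with diabetes and severe neuropathy, a large share of both arms may have at least one event. A yes/no variable near its ceiling has little room to show a difference, however far the event rates differ.

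Follow-up is the second issue. A patient who leaves early has had less time for a first event, and a logistic model without a follow-up term treats that patient as fully observed. The ulcer analysis avoids this: Cox regression handles unequal follow-up, and Primary outcome measure also counts the total number of ulcerations. General AEs and SAEs get neither, and no reason is given.

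At stake is how a null result is read. A non-significant odds ratio for pooled AEs could be taken as evidence of no safety difference when the test had little power to find one.

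**Working it through.** **Inputs.** From Sample size: 150 per arm, 20% dropout over two years, two-sided 5%. From Study design: 1:1 allocation. From Primary outcome measure: 24 months. The documents give no AE or SAE rate, no between-patient variation and no safety power, so there is no stated figure to reproduce; the "type I error probability of 5% (two-sided) and a power of 80" per cent concern ulceration only. Assumed here: control rates of 0.05 to 3 events per patient-year, a true rate ratio of 1.4 or 1.5, and gamma-distributed rates between patients with variance k of 0 to 1.5.

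**Step 1, closed form with full follow-up.** Let μ be the mean number of events per control patient over 24 months (μ = 2 × yearly rate), μ′ = rate ratio × μ, and n = 150 per arm. For k = 1:

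- Yes/no: p = μ/(1 + μ), p′ = μ′/(1 + μ′), then the two-proportion test.
- Rate: SE(log rate ratio) = √[(1/μ + k + 1/μ′ + k)/n]; power = Φ(log rate ratio/SE − 1.96).

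Worked example, 1 event per year, rate ratio 1.4: μ = 2, μ′ = 2.8.

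- Yes/no: p = 0.667, p′ = 0.737, difference 0.070. Null SE = √(2 × 0.702 × 0.298/150) = 0.0528. Alternative SE = √[(0.222 + 0.194)/150] = 0.0527. Power = Φ[(0.070 − 1.96 × 0.0528)/0.0527] = Φ(−0.63) = 26%.
- Rate: SE = √[(0.5 + 1 + 0.357 + 1)/150] = 0.138. Power = Φ(0.336/0.138 − 1.96) = Φ(0.48) = 68%.

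**Step 2, simulation with 20% exponential dropout** (rate ratio 1.4, variance 1.0; rate test with person-time and robust variance):

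| Control events per patient-year | Yes/no power | Rate-test power | Share of rate-test power kept |
|---|---|---|---|
| 0.05 | 13% | 14% | 13/14 = 93% |
| 0.25 | 26% | 39% | 26/39 = 67% |
| 0.5 | 27% | 54% | 27/54 = 50% |
| 1 | 25% | 65% | 25/65 = 38% |
| 3 | 15% | 75% | 15/75 = 20% |

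With equal dropout and no true difference, both tests reject in about 4–6% of trials. Other variances move the levels but not the pattern. At 0.25, 0.5 and 1 per year, variance 0.5 gives 34/47, 41/68 and 34/84%, and variance 1.5 gives 23/35, 24/45 and 21/55%. In all three, the yes/no test falls below half of the rate test's power between 0.5 and 1 per year.

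**Step 3, a second effect size** (rate ratio 1.5, closed form). With k = 1: μ = 0.2 gives 28% vs 34%, μ = 1 gives 41% vs 74%, μ = 4 gives 26% vs 89%. With no extra variation between patients (k = 0) the loss starts later: 73% vs more than 99% at μ = 2, and 27% vs more than 99% at μ = 4.

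**Step 4, unequal follow-up.** Assume no true difference, k = 1, and dropout of 10% in one arm and 30% in the other. With exponential dropout d over two years and hazard g = −ln(1 − d)/2, mean follow-up is d/g: 0.1/0.0527 = 1.90 years against 0.3/0.178 = 1.68 years. At rates of 0.25 to 3 per year the yes/no test then rejects in about 8–16% of trials, and the person-time rate test in about 4–6%. When few patients have any event, the shorter follow-up hardly changes the share affected.

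**The case against.** Four points count against a stronger version, and most of their substance stands.

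- A reader might infer that the analysis contradicts the stated endpoint. The documents do not support that. In safety reporting, frequency can mean the share of patients with an event, which is what the logistic model compares. It is a poor fit for repeated events, not a contradiction.
- A reader might infer that this is the only between-arm comparison of harm. It is not: foot precursors, partly drawn from AE reports, are compared by Cox regression, and AEs and SAEs are set out by arm and risk class. The plan also refers to models in the plural and to types of event, so analyses by type are possible; single types would fall in the low-rate range, where little is lost.
- The gain from counts assumes that harm multiplies the event rate. If it mainly brings more patients to a first event, the yes/no analysis loses little.
- The strongest point is ascertainment. The trial is open-label, and the intervention arm has twice-daily measurements, a diary, photo requests and alarm-triggered visits; controls have six-monthly visits and consultations they start themselves. If surveillance alone raised recorded events 1.4-fold (an assumption), power would become the rate of false signals: at variance 1.0 and 0.25 to 3 events per year, 39–76% for the rate test against 16–27% for the yes/no test. This is a good reason not to replace the patient-level comparison.

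It could also be said that rates belong in an SAP. But the article itself fixes the model, the target and the covariates, so whether that choice is good is a fair question. None of these points restores the repeat events or the follow-up time that the comparison drops.

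**Conclusion.** The point holds in a limited form. For general AEs and SAEs, the one formal comparison discards repeat events and makes no allowance for unequal follow-up, although 20% dropout is expected.

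The size depends on a rate that the documents do not give. At rate ratio 1.4 and variance 1.0, almost nothing is lost at 0.05 events per patient-year, about a third of the rate test's power at 0.25, and more than half only from about 0.5 to 1 per year upward. With no extra variation between patients the loss starts at higher rates. It is tempting to say that the planned test saturates and loses most of its power in general. That is not supported: it would be wrong for rare events, as SAEs may be, and is plausible mainly for all AEs pooled.

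The inflated rejection rate of 8–16% rests on an assumed dropout of 10% vs 30%; the documents do not predict unequal dropout.

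Nothing in the article says that a non-significant odds ratio will be read as proof of safety, but for pooled AEs it should not be. This is a secondary analysis and the remedy is a cheap improvement.

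**What to change.** Keep the logistic model. Add to Statistical analysis, Secondary endpoints, for AEs and separately for SAEs:

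- events per patient-year by arm;
- a comparison of the number of events per patient by negative binomial regression (or Poisson regression with robust standard errors), with log follow-up time as offset and the same covariates as the logistic model;
- the rate ratio with its 95% confidence interval.

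Add a sentence that the rate ratio is read beside the patient-level result, because closer surveillance of the intervention arm can raise recorded counts, and that a non-significant odds ratio for pooled AEs is not evidence of no safety difference.

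The cost is analysis wording and one more regression each for AEs and SAEs, with no new data and no more patients. The downside is that patients with many events weigh more, which the overdispersion term or robust variance takes into account in the standard errors. The surveillance bias is not removed by the model and has to be handled in interpretation.
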